
### Sample size calculation

We used GPower3.1.9.2 to perform the power calculation. Our primary outcome measure is the motor quotient measured on the PDMS-II. A difference of the motor quotient score among the three groups of 0.5 SD is considered to be clinically significant. Thus, we must recruit 42 infants in each group to have an 80% chance of detecting this difference among the three groups with a significance level of 0.05 (alpha) on two-sided tests. Considering potential attrition, 49 infants in each group will be recruited.

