## Study design

The CHD patients with cardiac catheterization will be recruited from and investigated at the Xin Hua Hospital affiliated to the Shanghai Jiao Tong University School of Medicine, Shanghai City, China.

Prior to inclusion, the following information will be obtained for all patients: demographic data (for example, gestational age at birth, birth weight, CA, and gender), medical history (for example, the duration of intensive care unit and hospital stay, and age of cardiac catheterization), heart defect (for example, defect type and size), and type of feeding (for example, breast or artificial feeding). Each patient’s parents will be asked to sign an informed consent form before the patient can participate in the study.

Eligible participants will be randomized by a 1:1:1 allocation ratio by computer either to the exercise intervention group, in which they will receive passive movement and active exercise to promote motor development; the home-based intervention group, in which they will receive passive movement and active exercise from parents or caregivers at home; or the control group, in which they receive follow up only (Fig. 1). The total study duration will be 23 months, which consists of a 3-month intervention and 20-month follow-up period without intervention. All patients will receive the exercise intervention, the home-based intervention, or the control conditions as allocated. All patients will be assessed at 1, 4, 6, 12 and 24 months CA.

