## Statistical analysis

The SPSS 20.0 and Microsoft Excel 2013 software will be used for statistical analyses. Demographic data will be described with descriptive statistics, including the mean ± standard deviation (SD). We will use analysis of covariance to compare the primary and secondary outcomes of the three groups. A general linear model will be used to compute mean outcome values adjusted for diagnosis, gender and socioeconomic status (SES), with the group as the fixed factor and diagnosis, gender and SES as covariates. If patients are lost to follow-up, an intention-to-treat analysis will be performed. Statistical significance is set at a p-value less than 0.05.

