## Discussion

According to previous studies, exercise is an effective treatment for adolescents and adults with CHD. However, the evidence of the effects of exercise for CHD infants with cardiac catheterization is sparse. We will perform a prospective randomized-controlled trial of passive movement and active exercise for very young CHD infants with cardiac catheterization. The chosen method seems safe, applicable and feasible to very young infants with CHD. The study may provide evidence that passive movement and active exercise offer an alternative treatment for very young infants with CHD. Passive movement and active exercise may have some beneficial effects for infants with CHD by promoting motor development and growth, and improving heart function and bone quality.

This study has some strengths. First, the follow-up duration in most previous exercise studies typically ranged from 12 weeks [23] to 1 year [20]. In this study, the total study period is 23 months, with an intervention duration of 12 weeks and a follow-up duration (with no active intervention) of 20 months. Second, in this study, the intervention group performs exercises with the assistance of experienced pediatric physiotherapists, meanwhile the home-based intervention group performs exercises with the assistance of parents or caregivers, but the control group receives no training. Therefore, compared to previous studies [18–20, 23], our study could reduce biases. Third, a power calculation is performed for this study. The total number of patients enrolled in the study is 147. Fourth, previous studies have mainly focused on exercise capacity [10, 18–20] and motor development [23]. Heart function and bone quality are rarely analyzed following passive movement and active exercises in patients with CHD. However, there are some limitations in our study. The spontaneous daily activities outside the study exercises are not monitored. Parents or caregivers may alter their infants’ daily activities, which would influence motor development.

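### 42 infants per group give about 51–64% power, not 80%, for the stated 0.5 SD difference in motor quotient

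*Protocol article*

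**What the plan says.** The Sample size calculation section of the protocol article fixes the effect size: "A difference of the motor quotient score among the three groups of 0.5 SD is considered to be clinically significant". It then states that "we must recruit 42 infants in each group to have an 80% chance of detecting this difference among the three groups". Alpha is set at 0.05, two-sided. The software is named ("We used GPower3.1.9.2 to perform the power calculation"), but not the test family, Cohen's f, the pattern of the three means, or any correlation or explained variance. The recruitment target follows: "Considering potential attrition, 49 infants in each group will be recruited", which is 147 in all.

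The Statistical analysis section names the test: "We will use analysis of covariance to compare the primary and secondary outcomes of the three groups". Its covariates are diagnosis, gender and SES; the baseline motor quotient is not among them. The Discussion counts the calculation among the study's strengths: "Third, a power calculation is performed for this study".

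**The concern.** The section gives effect size, alpha, sidedness, power and number of groups, which is enough to check the result once a pattern of means is chosen. A 0.5 SD difference between two groups at two-sided 0.05 and 80% power is a standard case that needs 64 per group, so 42 looks too small at once. A three-group test can need somewhat fewer or considerably more, depending on where the third mean lies, but not as few as 42.

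This is the power statement for the primary outcome. If the true power is well below 80%, a non-significant result says much less about the absence of a 0.5 SD effect than readers of the article would suppose.

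**Working it through.** **Inputs.** From the Sample size calculation section: difference 0.5 SD, alpha 0.05 two-sided, power 0.80, n = 42 evaluable per group, 49 recruited. From the Study design section: three groups allocated 1:1:1, so N = 3 × 42 = 126. The pattern of means is not stated, so both extreme patterns with a largest difference of 0.5 SD are used.

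**Attrition step.** 1 − 42/49 = 14.3%, and 42/(1 − 1/7) = 49. This step is consistent; the problem is the 42.

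**Pairwise t test.** Noncentrality = d × √(n/2), df = 2n − 2.
- n = 42: 0.5 × √21 = 2.291, df = 82, critical t = 1.989. Power = 62.0%.
- n = 63 gives 79.5% and n = 64 gives 80.1%, so 64 per group are needed.
- n = 42 with alpha 0.025 (two contrasts, Bonferroni): power 50.6%.

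**Three-group F test.** Cohen's f = (SD of the three means, divisor 3)/(within-group SD); noncentrality λ = f² × N; df = 2 and N − 3. At N = 126 the critical F is 3.07.
- Third group midway (0, 0.25, 0.5): f = 0.5/√6 = 0.204, λ = 5.25.
- Third group equal to one extreme (0, 0, 0.5): f = 0.5 × √2/3 = 0.236, λ = 7.00. For a largest difference of 0.5 SD this is the most favourable pattern.

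| Reading of 0.5 SD (two-sided 0.05) | n/group for 80% | Power at 42/group | Power at 49/group |
|---|---|---|---|
| F test, third group midway (f = 0.204) | 79 | 51.4% | 58.4% |
| Pairwise t test | 64 | 62.0% | 68.8% |
| F test, one group differs (f = 0.236) | 59 | 64.4% | 71.7% |
| F test, generic f = 0.25 | 53 | 69.9% | 77.1% |
| F test, steps of 0.5 SD (0, 0.5, 1) | 21 | 98.7% | 99.5% |
| F test, 0.5 entered as f | 14 | 99.9% | >99.9% |

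No row returns 42 per group. A one-sided t test, which contradicts the stated sidedness, needs 51 and has 73.5% power at 42. Charging up to four covariates that explain no variance changes power by less than 0.1 percentage point.

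**What 42 per group does detect with 80% power.** For the F test, f = 0.280: a largest difference of 0.280/0.471 = 0.59 SD if one group differs, or 0.280/0.408 = 0.69 SD if the means are evenly spaced (0.471 and 0.408 are f for a largest difference of 1 SD). For one pairwise test, 0.62 SD.

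**Where 42 may have come from.** With f = 0.5, the F test returns a total of 42 (14 per group, power 80.3%). The 0.5 SD may have been entered as f and the total read as a per-group number. This is an inference, and nothing in the conclusion depends on it.

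**The case against.** The strongest reply is that the 51–64% range is conditional. It assumes one time point, covariates that explain nothing, and a largest gap of 0.5 SD. Each can be questioned.

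- **Covariates.** The planned model is an ANCOVA. If the covariates explained 30% of the variance (an assumption), power at 42 per group would be 80.5% at f = 0.236 and 77.2% pairwise, though only 67.6% at f = 0.204. At 20% explained, the figures are 74.7%, 71.6% and 61.4%.
- **Repeated measures.** The motor quotient is measured at five ages. A between-group repeated-measures F test returns exactly 42 per group for some inputs, such as f = 0.204 with five measures and a correlation of 0.4, or f = 0.236 with four measures and a correlation of 0.6.
- **Other readings of 0.5 SD.** Steps of 0.5 SD between successive groups, or f = 0.5, would put power above 98%.
- **Condensed text.** The article may omit software settings that the full protocol records.

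What stands is that the range depends on the reading, so the repair should begin by stating the assumptions. What does not stand is the 80% claim as printed. The variance-reduction and repeated-measures routes need an R-squared or a correlation the article does not give, and the second also needs a model other than the group-factor ANCOVA it describes. The readings that exceed 80% would need 21 or 14 per group, so they do not explain 42 either. The conventional f = 0.25 still leaves power at 69.9%.

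**Conclusion.** The concern holds. From the inputs the article states, 42 per group does not give 80% power for a 0.5 SD difference. Power is 62% for one pairwise comparison and 51–64% for the three-group test, so the chance of missing the difference is about 36–49% rather than 20%. The attrition allowance does not rescue the claim, since full retention of 49 per group reaches at most 71.7% when the largest difference is 0.5 SD.

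These figures assume that 0.5 SD is the largest difference between group means, that the outcome is analysed at one time point, and that the covariates explain no variance. An unstated correlation or model could alter them, but it would have to be written down and justified. Because this statement supports the primary outcome and the calculation is presented as a strength, it must be corrected.

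**What to change.** State the test, the assumed pattern of means (or f), and any correlation or explained variance that was used. If none was used, replace the 80% claim with wording such as: 42 evaluable infants per group give about 62% power for a 0.5 SD pairwise difference (51–64% for the three-group test, depending on the pattern of means); 80% power is reached at about 0.62 SD pairwise, or 0.59–0.69 SD for the three-group test. Qualify the Discussion's reference to the power calculation to match.

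If the 1-month motor quotient is added as a covariate, state the assumed correlation with the 24-month value. With power depending on 0.5/√(1 − r²), about r = 0.59 would restore 80% for the pairwise comparison, and 0.54 to 0.68 for the three-group test.

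The cost is a wording change and a less favourable power statement. No extra infants are needed. Keeping 80% power at 0.5 SD without such a covariate would instead mean 59, 64 or 79 evaluable per group, which at the same 14.3% attrition is 69, 75 or 93 recruited per group against the 49 planned.

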## Statistical analysis

The SPSS 20.0 and Microsoft Excel 2013 software will be used for statistical analyses. Demographic data will be described with descriptive statistics, including the mean ± standard deviation (SD). We will use analysis of covariance to compare the primary and secondary outcomes of the three groups. A general linear model will be used to compute mean outcome values adjusted for diagnosis, gender and socioeconomic status (SES), with the group as the fixed factor and diagnosis, gender and SES as covariates. If patients are lost to follow-up, an intention-to-treat analysis will be performed. Statistical significance is set at a p-value less than 0.05.

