## Participants

CHD patients with cardiac catheterization are eligible for the study. Patients who meet the following inclusion criteria will be enrolled:infants with CHD,less than 1 month CA,with a modified Ross score of less than 3 points,availability 5 days a week over a period of 12 weeks,for whom informed parental consent has been provided.

Patients who have any of the following exclusion criteria will be excluded:previous cardiac operation history;a genetic syndrome, respiratory failure, neurological disorder, or arrhythmia;heart failure with a modified Ross score of 3 points or more;significant hemodynamic defects to make exercises inadvisable; orother congenital malformations.

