## Withdrawal management

The patients with CHD who have any of the following conditions will be allowed or will be asked to withdraw from the study:The patient’s parents require withdrawal.The patient develops heart failure, or respiratory failure, or other serious diseases.The exercises lead to any adverse effects.

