### Secondary outcome measures

The Ross score will be evaluated using a modified Ross scoring system. The Ross scoring system [48] was first described by Ross [49] for infants. Then, Reithmann et al. [50] and Läer et al. [51] modified the system. The modified Ross scoring system is used in the clinical evaluation of patients with CHD. It consists of diaphoresis, tachypnea, breathing with abdominal retractions, respiratory rate, heart rate, and hepatomegaly. Each variable receives a score of 0, 1, or 2 points according to severity. The range of the total score is from 0 to 12 points with higher values indicating more severe impact. An experienced pediatric cardiologist grades the six variables.Ventricular function will be assessed using echocardiography, which is a useful noninvasive method. In patients with CHD, the measurement of ventricular function using echocardiography is a standard procedure [52]. The left ventricular function is an important variable. The most commonly utilized indices of the left ventricular function are the left ventricular ejection fraction and fractional shortening [48]. Echocardiographic assessment of the patients is performed by an experienced pediatric cardiologist. Echocardiographic assessment of crying children is performed approximately 5 minutes after they become calm.Bone quality will be measured using a quantitative ultrasound machine (Omnisense 7000P, Sunlight Medical Inc., Israel). Quantitative ultrasound measurements provide a safe, non-invasive method for obtaining information on bone quality. The quantitative ultrasound method is designed to measure the speed of sound (SOS) at a peripheral site (such as the distal 1/3 of the radius and middle of the tibia [53]) by axial transmission. The measurement site is defined as the distal 1/3 of the radius. The mean of three measurements of the radius SOS is used for analysis. The z-score is given in terms of the standard deviation from the average of population of same age and gender. The z-score is defined as the difference between the raw score to be standardized and the mean difference divided by the standard deviation (a z-score less than or equal to −2.0 indicates low bone quality and a z-score greater than −2 indicates normal bone quality). The z-score is predictive of bone quality in children [54, 55]. All quantitative ultrasound measurements are performed by the same trained pediatrician.Anthropometric measurements, including body length, weight, head circumference and upper arm circumference, will be measured. Body length is measured without shoes. Weight is measured with light clothing using digital scale (Seca Digital Column Scale and Seca 376 Baby Scale). Head circumference and upper arm circumference are measured with a nonflexible tape.Adverse events related to exercise will be recorded.

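### Withdrawal on heart failure can remove the Ross scores that would show cardiac harm, which biases the planned comparison of means toward no harm

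*Protocol article*

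**What the plan says.** The Statistical analysis section of the protocol article sets one method for all outcomes: "We will use analysis of covariance to compare the primary and secondary outcomes of the three groups". The adjustment covariates are diagnosis, gender and socioeconomic status.

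The modified Ross score is a secondary outcome, built from six items scored 0, 1 or 2: "The range of the total score is from 0 to 12 points with higher values indicating more severe impact". Under Participants, infants enter "with a modified Ross score of less than 3 points", and the exclusions include "heart failure with a modified Ross score of 3 points or more".

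Under Withdrawal management, infants with any of three listed conditions "will be allowed or will be asked to withdraw from the study". One condition is "The patient develops heart failure, or respiratory failure, or other serious diseases". Another is "The exercises lead to any adverse effects".

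On incomplete follow-up the Statistical analysis section says only: "If patients are lost to follow-up, an intention-to-treat analysis will be performed". The aims under Methods/Design include potential adverse effects of the exercise. Assessments are set at 1, 4, 6, 12 and 24 months corrected age.

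**The concern.** A rise in the Ross score is one of the ways in which cardiac deterioration would appear in this trial. The infants whose scores rise most are those who develop heart failure, and these are the infants whom the withdrawal rule may take out of the study, not merely out of the exercise programme. Whether a later score exists then depends on what that score would have been. If exercise did raise the risk of heart failure, the loss would also differ by arm. The criterion on adverse effects of the exercises adds to the imbalance, because only infants who receive the exercises can meet it.

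What is at stake is false reassurance. The adjusted Ross means could look alike across the three groups because the affected infants are no longer among those averaged, and a reader could take that as evidence of cardiac safety in very young infants.

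**Working it through.** **What the plan gives.** It has no figure for the Ross score or for harm, so there is nothing to reproduce on this point. The one design input taken from it is 49 infants per group (Sample size calculation).

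**Assumptions, not in the documents.** Infants without heart failure score 0, 1 or 2 with probabilities 0.60, 0.25 and 0.15 in every arm. Infants with heart failure score 3 to 7 with equal probability. The heart-failure rate is 5% in control and 15%, 20% or 30% with exercise. Covariates are ignored.

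**Expected means.**
- Without failure: 0.25 × 1 + 0.15 × 2 = 0.55.
- With failure: (3 + 4 + 5 + 6 + 7)/5 = 5.
- Arm mean at failure rate p with all scores kept: 0.55(1 − p) + 5p = 0.55 + 4.45p.
- Difference at 20% against 5%: 4.45 × 0.15 = 0.67. At 30% against 5%: 4.45 × 0.25 = 1.11.
- Difference if every failure is dropped: 0.55 − 0.55 = 0 at any p.

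The zero in the last line follows from giving the retained infants the same distribution in each arm. It shows how the bias arises; it does not estimate its size in this trial.

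**Simulated rejection rates, one exercise arm against control, 49 per arm, two-sided 0.05.**

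| Heart failure, exercise v control | Means, failures dropped | Means, half of failures keep a score | Means, all scores kept | Rank test, all scores kept | Fisher test on failure, all randomised |
|---|---|---|---|---|---|
| 15% v 5% | 5% | 14% | 28% | 15% | 24% |
| 20% v 5% | 5% | 25% | 49% | 28% | 49% |
| 30% v 5% | 5% | 55% | 86% | 65% | 89% |

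**Three-arm check**, with the failure rate raised in both exercise arms and a one-way F test. With failures dropped, rejection stays near 5% throughout. Carrying a pre-failure score forward also gives about 5%. With all scores kept it is 25%, 48% and 87% at 15%, 20% and 30%. A chi-square test of failure incidence in all randomised infants gives 35%, 63% and 95%. At 10% against 5% every approach is weak: 9% for means with all scores kept and 12% for incidence.

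**Reading the results.** The large step lies between dropping the failures and keeping them. With the same infants kept, a two-arm comparison of means does about as well as the Fisher test and better than a rank test. The choice of model is therefore not what hides the harm.

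**The case against.** A reader might infer that analysis of covariance cannot show cardiac harm because entry confines the score to 0 to 2. The documents do not support that. The limit governs enrolment only. The outcome runs to 12, which leaves at least 10 points in which to worsen, so a low starting score restricts the detection of benefit rather than of harm. The table shows that a comparison of means detects harm when the scores are present.

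The withdrawal wording is also softer than compulsory removal, since infants are allowed or asked to leave. It does not define heart failure by a Ross score; the link to 3 points appears only in the exclusion criterion. An infant who scores 3 at a visit is not removed for that alone. If half of the failures keep a score, part of the power returns.

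The protocol also promises intention-to-treat, measures ventricular function by echocardiography and records adverse events related to exercise. The method for missing values may sit in an analysis plan that is not shown.

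Much of this stands and limits the point to a bias. It does not remove it. An intention-to-treat label cannot supply scores that were never taken, and carrying forward a score from before the failure leaves rejection near 5%. Withdrawn infants may lose later echocardiography as well, and recording only exercise-related events gives no fair comparison with a control group that does not exercise. The problem comes from two rules that the article itself states, not from detail that it leaves out.

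**Conclusion.** The point holds as a bias toward no cardiac harm, not as an impossibility of showing harm. It arises because a stated withdrawal rule can make Ross scores missing as a result of the outcome being compared.

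Under the assumed rates of 5% and 20% with 49 per group, the comparison of means rejects about 5% of the time if every failure leaves without a later score, about 25% if half keep one, and about 49% if all do. The heart-failure rates and score distributions are assumptions, and the first figure is the extreme case. How close the trial comes to it depends on how many infants with heart failure actually leave and whether a score is taken when they do. Replacing analysis of covariance is a matter of preference and would not by itself cure the problem.

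**What to change.** Keep the analysis of covariance and add one comparison by randomised arm: the proportion of infants with a Ross score of 3 or more at follow-up or withdrawn for heart failure, with all randomised infants in the denominator and such withdrawals counted as events. An exact test or a logistic model would serve. The 3-point threshold is the one that the exclusion criterion already uses.

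Record the reason for withdrawal and the Ross score at that time, and continue the scheduled outcome assessments in withdrawn infants where parents agree. State in the Statistical analysis section how these infants enter the intention-to-treat analysis. None of this changes the clinical criteria for withdrawal.

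The cost is a small added data item and some follow-up effort, so it is slightly more than a change of wording; the article does not say that reason and score at withdrawal are now captured. The binary measure ignores differences within 0 to 2, which is why it should accompany the score analysis. Recruitment is underway, so scores not taken at withdrawal in the meantime cannot be recovered.

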### Methods/Design

A prospective and randomized controlled trial involving passive movement and active exercise in very young CHD infants with cardiac catheterization will be performed. The aim of the study is to determine:whether passive movement and active exercise beginning at 1 month of corrected age (CA) in infants with CHD improves motor development at 24 months of CA compared with control subjects,the potential benefits of exercise on growth, heart function and bone quality of very young infants with CHD, andthe potential adverse effects related to passive movement and active exercise.

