## Randomization process

The participants are randomly assigned to each group after the baseline assessment, when the demographic data are collected. We use concealed randomization assignment and an adequate computer-generated assignment sequence to avoid selection bias. Thus, neither investigators nor the participants’ parents can influence which group the patients are assigned to.

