### Primary outcome measure

Motor development will be measured using the Peabody Developmental Motor Scales-II (PDMS-II) via the motor quotient. Motor development is measured at 1, 4, 6, 12 and 24 months CA with the PDMS-II by an assessor blinded to the group assignments. The use of the PDMS-II is recommended [40] and has been widely used as a motor development outcome measure for patients with CHD [41–46]. Both fine and gross motor function can be assessed by the PDMS-II. The PDMS-II is valid for children aged from term to 76 months. The PDMS-2 contains six subtests, including reflexes, stationary, locomotion, object manipulation, grasping and visual-motor integration. The results of the subtests may be used to generate a Gross Motor Quotient, a Fine Motor Quotient and a Total Motor Quotient, which are three global indices of motor development. A previous study demonstrated that the PDMS-II had high test-retest reliability and acceptable responsiveness to intervention effects [47].

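### The adjusted comparison omits the 1-month motor quotient, which is measured before randomization, and so gives up precision that needs no new data

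*Protocol article*

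**What the plan says.** All references are to the protocol article.

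- **Method (Statistical analysis).** "We will use analysis of covariance to compare the primary and secondary outcomes of the three groups". The next sentence describes a general linear model giving adjusted means, "with the group as the fixed factor and diagnosis, gender and SES as covariates". No baseline value of any outcome is named, here or elsewhere.
- **Primary outcome (Sample size calculation).** "Our primary outcome measure is the motor quotient measured on the PDMS-II".
- **Visits (Primary outcome measure).** "Motor development is measured at 1, 4, 6, 12 and 24 months CA with the PDMS-II". The Outcome measures section gives the same five ages for the baseline and follow-up evaluations generally.
- **Order of events (Randomization process).** "The participants are randomly assigned to each group after the baseline assessment".
- **Time point of interest (Methods/Design).** The first aim asks whether the exercise "improves motor development at 24 months of CA compared with control subjects".
- **Planned size (Sample size calculation).** "A difference of the motor quotient score among the three groups of 0.5 SD is considered to be clinically significant", and "we must recruit 42 infants in each group to have an 80% chance of detecting this difference among the three groups". That calculation mentions neither covariates nor a correlation.

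**The concern.** The trial will hold, for every infant, a value of the primary outcome taken before allocation and on the same scale. A baseline measurement of the outcome is a natural covariate in an analysis of covariance. The article names an adjustment set and leaves this variable out, so it is a stated choice and not just a detail deferred to an analysis plan. An analysis plan that followed the article would carry the omission forward.

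What is at stake is efficiency. Variation in early motor level that persists to later visits stays in the residual, so confidence intervals are wider and tests weaker than the planned data allow. The same holds for the continuous secondary outcomes with a 1-month value: ventricular function, bone speed of sound, body length, weight and the two circumferences.

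**Working it through.** **Inputs from the article:** target difference 0.5 SD, 42 evaluable infants per group (126 in total), two-sided alpha 0.05, claimed power 80%.

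**Input not in the article:** r, the correlation of the 1-month motor quotient with the later one. Assumed range 0.1 to 0.6.

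**1. The plan's own figure.** For two groups, the noncentral t has 2 × 42 − 2 = 82 degrees of freedom and noncentrality 0.5 × √(42/2) = 2.29. Power is 62.0%, and 80% needs 64 per group. For the three-group F test, a 0.5 SD range between the extreme groups gives Cohen's f of 0.204 (third group midway) to 0.236 (two groups equal), with power of 51% to 64% at 126 infants. The stated 80% is not reproduced either way. That is a separate problem in the Sample size calculation; 62% serves here only as the starting point.

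**2. Effect of adding baseline.** Residual variance is multiplied by 1 − r², so the standardized difference becomes d = 0.5/√(1 − r²) and the noncentrality is d × √(42/2).

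| r | 1 − r² | d | Noncentrality | Pairwise power, 42 per group |
|---|---|---|---|---|
| 0 | 1.00 | 0.500 | 2.29 | 62.0% |
| 0.1 | 0.99 | 0.503 | 2.30 | 62.4% |
| 0.2 | 0.96 | 0.510 | 2.34 | 63.7% |
| 0.3 | 0.91 | 0.524 | 2.40 | 66.0% |
| 0.4 | 0.84 | 0.546 | 2.50 | 69.5% |
| 0.5 | 0.75 | 0.577 | 2.65 | 74.4% |
| 0.6 | 0.64 | 0.625 | 2.86 | 80.8% |

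The degree of freedom spent on baseline is ignored in this table; its effect is negligible. For the three-group test at f = 0.236, with that degree of freedom charged, power goes from 64% (r = 0) to 69% (r = 0.3), 78% (r = 0.5) and 84% (r = 0.6).

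**3. What adjustment cannot do.** To reach 80% with 42 per group by adjustment alone, r must be about 0.58 for the pairwise comparison, and about 0.54 (f = 0.236) to 0.69 (f = 0.204) for the three-group test.

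**4. Chance imbalance.** The standard error of a baseline difference between two groups of 42 is √(2/42) = 0.22 SD. At r = 0.5, an imbalance of that size shifts the unadjusted difference by about 0.5 × 0.22 = 0.11 SD. The unadjusted standard error already allows for this, so it is the same loss of precision seen from another side and not an extra error.

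**The case against.** **The list may not be closed.** The sentence on analysis of covariance names no covariates; the three variables appear in the next sentence, on adjusted means. If these are two models, the first could include baseline, with the detail left to the full plan. That reading is possible. The natural one is that the second sentence specifies the model for the first, and either way the article never names baseline. One added phrase would settle it.

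**The gain may be trivial.** This stands as a limit on size. The main aim is at 24 months, 23 months after baseline, and r could be low over that interval. At r of 0.1 or 0.2 the gain is 0.4 or 1.7 percentage points; at 0.3 it is about 4. Nothing in the article allows a choice within the range. The table also compares with a model that has no covariates. Diagnosis, gender and SES may already explain part of what baseline would, so the partial correlation is what counts.

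**Readings to avoid.** A reader might infer that leaving baseline out biases the comparison. It does not: the groups are randomized and the test is valid. A reader might also infer, from diagnosis being called a covariate in an SPSS general linear model, that a straight line will be fitted through arbitrary diagnosis codes. The article gives neither the coding nor the number of categories, and covariate is ordinary usage for any adjustment variable. With two categories, factor and covariate entry give the same fit. This supports a request for clarification and no more.

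**Conclusion.** The point holds as one of efficiency. The named adjustment set leaves out the pre-randomization value of the outcome, which the trial already plans to collect. The analysis as written is valid and unbiased but gives up precision.

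The size depends on a correlation the article does not give. Over an assumed r of 0.1 to 0.6, pairwise power for 0.5 SD with 42 per group moves from 62% to between 62.4% and 81%. For the 24-month comparison the lower part of that range may apply.

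A reader might conclude that baseline adjustment makes good the shortfall against the claimed 80%. That would need r of about 0.54 to 0.69, depending on the comparison, and the article offers no support for such a value. The power statement needs its own correction.

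**What to change.** - In the Statistical analysis section, add the 1-month corrected-age motor quotient as a covariate in the primary analysis of covariance, keeping diagnosis, gender and SES.
- For each continuous secondary outcome, add its own 1-month value to its model. Expect little gain for the Ross score, because entry requires a score below 3 and baseline is therefore confined to 0 to 2 on a 0 to 12 scale.
- As a clarification only, state that diagnosis is entered as a categorical factor if it has more than two unordered categories.

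The cost is a sentence in the analysis section and one degree of freedom per model for baseline, plus the degrees of freedom for the diagnosis categories if there are several. No new data are needed. The Trial status section says recruitment is under way, so the change should be recorded before any comparison by group is made.
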